***Review of [Assessment Tool/Worksheet] (Clinicians and FCP)***

Instructions: Please answer the following questions about the [assessment tool/worksheet] and ways we can make it better.

1. Did you have any issues accessing or viewing the [tool/worksheet]?
   1. No
   2. Yes (please explain)
2. How helpful was the [assessment tool/worksheet]?
   1. Not at all helpful
   2. Slightly helpful
   3. Moderately helpful
   4. Helpful
   5. Very Helpful
3. Please indicate what you found helpful about the [tool/worksheet].
4. How can we improve the [tool/worksheet]?
5. How difficult was it for you to understand the content of the [assessment tool/worksheet] (e.g. language, ideas)?
   1. Very difficult
   2. Difficult
   3. Moderately difficult
   4. Slightly difficult
   5. Not at all difficult
6. I am going to list a few things that may have made the video difficult to understand. Indicate whether each option made the video difficult for you. Was the video difficult because the:
   1. Wording was too complicated: Y/N
   2. Ideas were too complicated: Y/N
   3. There was too much information: Y/N
   4. There was not enough information: Y/N
   5. Other: __________________________: Y/N
7. If you found the content too easy or too simple, what made it too easy?
8. How helpful was the video in explaining how to use the [tool/worksheet]?
   1. Very helpful
   2. Somewhat helpful
   3. Neither helpful nor unhelpful
   4. Somewhat unhelpful
   5. Not at all helpful
9. Do you think it is necessary to watch the video in order to use the [tool/worksheet] correctly? Why or why not?
10. How confident would you be using the [tool/worksheet] without having seen the video?

a. Not confident at all

b. Not very confident

c. Somewhat confident

d. Confident

e. Very confident

Why do you think that?

1. [clinicians only] How likely are you to use the information [assessment tool/worksheet] in your clinical practice?
   1. Very Unlikely
   2. Unlikely
   3. Neutral
   4. Likely
   5. Very likely

11a. Why or why not?

1. Overall, how satisfied are you with the [assessment tool/worksheet]?
   1. Very dissatisfied
   2. Dissatisfied
   3. Neutral
   4. Satisfied
   5. Very Satisfied

***Review of Overall Intervention (Clinicians only)***

1. Overall, how helpful do you think the videos and [tool/worksheet] would be for you to help in providing care and support to your loved one or patients with memory problems?
   1. Not at all helpful
   2. Slightly helpful
   3. Moderately helpful
   4. Helpful
   5. Very Helpful
2. What are additional topics you think should be covered in the videos and [tool/worksheet]?
3. Regarding the amount of information in the videos ad [tool/worksheet], do you think there is:
   1. Too much information
   2. The right amount of information
   3. Not enough information
4. What additional information do you think should be included in the videos and [tool/worksheet]?
5. Overall, how satisfied are you with the intervention (videos and [assessment tool/worksheet] together)?
   1. Very dissatisfied
   2. Dissatisfied
   3. Neutral
   4. Satisfied
   5. Very Satisfied
6. Please provide any other general comments about the [videos and] [tool/worksheet].

# Aims 2 and 3. Feasibility and Acceptability.

***Post-intervention (to be completed at end of study enrollment)***

***Family Care partner***

1. How often did you use the [assessment tool/worksheet] with a hospice nurse or social worker?

4 times 3 times 2 times 1 time

□ I did not use the [assessment tool/worksheet] with a hospice nurse or social worker.

1. Which hospice team member used the [assessment tool/worksheet] with you?

□ Nurse

□ Social worker

□ Nurse and social worker

□ Don’t know

□ The hospice team did not use the [assessment tool/worksheet] with me

□ Other (specify):

1. About how long did it take you to use the [assessment tool/worksheet] with the hospice team member for the first time?

minutes

1. About how long did it take you to use the [assessment tool/worksheet] with the hospice team member during follow-up visits?

minutes

1. How helpful was the [assessment tool/worksheet]?
   1. Not at all helpful
   2. Slightly helpful
   3. Moderately helpful
   4. Helpful
   5. Very Helpful

5a. What about the [assessment tool/worksheet] did you find helpful?

5b. What about the [assessment tool/worksheet] did you find least helpful?

1. How difficult was it to use the [assessment tool/worksheet]?
   1. Very difficult
   2. Difficult
   3. Moderately difficult
   4. Slightly difficult
   5. Not at all difficult

6a. What about the [assessment tool/worksheet] was easy to use?

6b. What about the [assessment tool/worksheet] made it difficult to use?

1. Overall, how satisfied are you with the [assessment tool/worksheet]?
   1. Very dissatisfied
   2. Dissatisfied
   3. Neutral
   4. Satisfied
   5. Very Satisfied
2. What about the [assessment tool/worksheet] could we change to make you more likely to use it?

***Clinicians***

1. How often have you used any of the information in the educational videos in your work with home hospice patients with dementia and their families?

□ Frequently: with most of my patients with dementia

□ Sometimes: with some of my patients with dementia

□ Rarely: with a few of my patients with dementia

□ Never: I have not applied any of the information from the videos in my clinical practice

1. I used the information in the educational videos with home hospice patients without dementia:]

□ Yes

□ No

1. Which parts of the educational videos did you use in your clinical practice (check all that apply)?

□ Main point of video 1

□ Main point of video 2

□ Main point of video 3

□ Main point of video 4

□ Other (specify):

1. Overall, how satisfied are you with the educational videos?
   1. Very dissatisfied
   2. Dissatisfied
   3. Neutral
   4. Satisfied
   5. Very Satisfied
2. With how many FCP did you use the [assessment tool/worksheet]?

0 1 2 3 4 >4

□ I don’t have any patients with dementia on my caseload.

1. About how long did it take you to use the [assessment tool/worksheet] with a family member for the first time?

minutes

1. About how long did it take you to use the [assessment tool/worksheet] with a family member during follow-up visits?

minutes

1. How helpful was the [assessment tool/worksheet] when working with family members?
   1. Not at all helpful
   2. Slightly helpful
   3. Moderately helpful
   4. Helpful
   5. Very Helpful

7a. What about the [assessment tool/worksheet] did you find helpful when using with family members?

7b. What about the [assessment tool/worksheet] did you find least helpful when using with family members?

1. How difficult was it to use the [assessment tool/worksheet] as part of your clinical practice? (reverse code)
   1. Very difficult
   2. Difficult
   3. Moderately difficult
   4. Slightly difficult
   5. Not at all difficult

9a. What about the [assessment tool/worksheet] was easy to use?

9b. What about the [assessment tool/worksheet] made it difficult to use?

1. Overall, how many times did you use the worksheet with each family member?
   1. 4 times
   2. 1- 3 times
   3. Not at all
2. You were asked to use the worksheet up to four times with each family member enrolled in the study. Did you find that to be
   1. Not enough times
   2. The right amount of times
   3. Too many times

11a. [If 11 is A or C] What is the ideal number of times the worksheet should be used with each family member?

11b. [If 11 is A or C] Please explain?

1. How likely are you to continue to use the [assessment tool/worksheet], now that the study has concluded?
   1. Very Unlikely
   2. Unlikely
   3. Neutral
   4. Likely
   5. Very likely

12a. Why or why not?

1. What about the [assessment tool/worksheet] could we change to make you more likely to use it?
2. What were the types of barriers you observed to implementing the steps family members identified through the [assessment tool/worksheet]? (check all that apply)

□ Family members did not take steps they agreed upon (please explain)

□ Interdisciplinary team dynamics impacted family members from implementing steps (please explain)

□ Other (please explain)

1. Overall, how satisfied are you with the [assessment tool/worksheet]?
   1. Very dissatisfied
   2. Dissatisfied
   3. Neutral
   4. Satisfied
   5. Very Satisfied
2. Was there anything that happened during the study that took you by surprise?
   1. No
   2. Yes (please explain).
3. Overall, how satisfied are you with the intervention (videos and [assessment tool/worksheet] together)?
   1. Very dissatisfied
   2. Dissatisfied
   3. Neutral
   4. Satisfied
   5. Very Satisfied

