# Aim 2 and 3 Feasibility and Acceptability: User-Centered Design

**Family Care partners and Clinicians**

***Review of Individual Videos (Clinicians Only-to be administered post video training)***

Instructions: Now we are going to ask you some questions about each video. Thinking about the video on (*state topic*) (repeat for each video)

1. Did you have any issues accessing or viewing the video on [topic]?
   1. No
   2. Yes (please explain)
2. How much of this video did you watch?
   1. 25%
   2. 50%
   3. 75%
   4. All of it
   5. None of it
3. If 2b or 2c: I did not complete the videos because (check all that apply).

□ I had trouble understanding the videos

□ The videos were too long

□ I did not think the content of the videos was relevant to my work

□ I did not learn anything from the videos

□ I did not have time to watch the videos

□ Other (specify):

1. How helpful was the video on [topic] to you?
   1. Not at all helpful
   2. Slightly helpful
   3. Moderately helpful
   4. Helpful
   5. Very Helpful
2. Please indicate what you found helpful about the video:
3. How could we improve the video?
4. How difficult was it for you to understand the content of the video on [insert /topic] (e.g. language, ideas)?
   1. Very difficult
   2. Difficult
   3. Moderately difficult
   4. Slightly difficult
   5. Not at all difficult
5. [If participant scores >1 on the previous item]: I am going to list a few things that may have made the video difficult to understand. Indicate whether each option made the video difficult for you. Was the video difficult because the:
   1. Wording was too complicated: Y/N
   2. Ideas were too complicated: Y/N
   3. There was too much information: Y/N
   4. There was not enough information: Y/N
   5. Other (please specify): __________________________: Y/N
6. If you found the content too easy or too simple, what made it too easy?
7. What information was provided that will help you [support family members with respect to [patients' eating and drinking/pain/]/record family members’ burden in the electronic health record/assess family members' burden, stressors or worries]?
8. What additional information could be provided to help you better [support family members with respect to [patient’s' eating and drinking/pain/]/record family members’ burden in the electronic health record/support family members to reduce their burden, stressors or worries]?

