9. What questions do you still have that would help you [support family members with respect to [patients' eating and drinking/pain/]/record family members’ burden in the electronic health record/support family members to reduce their burden, stressors or worries]?
10. How likely are you to use the information from the video on [topic] in your clinical practice?
    1. Very Unlikely
    2. Unlikely
    3. Neutral
    4. Likely
    5. Very likely

13a. Why or why not?

1. Overall, how satisfied are you with the video on [topic]?
   1. Very dissatisfied
   2. Dissatisfied
   3. Neutral
   4. Satisfied
   5. Very Satisfied

Instructions: Thinking about all of the videos, please answer the following questions.

*[questions 15-18 for aim 3 only]*

1. How did you watch the videos? Check all that apply.
   1. Phone
   2. Computer
   3. Tablet
   4. Other (please specify)
2. What is your preferred method of watching the videos?
   1. Phone
   2. Computer
   3. Tablet
   4. Other (please specify)
3. How difficult was it to view the videos using your preferred method?
   1. Very difficult
   2. Difficult
   3. Moderately difficult
   4. Slightly difficult
   5. Not at all difficult
4. Where were you when you were watching the videos? Check all that apply.
   1. At home
   2. Place of work
   3. During commute
   4. Car
   5. Other (please specify)
5. Who do you think it the appropriate audience for these videos? (check all that apply)
   1. Family members
   2. Hospice nurses
   3. Hospice social workers
   4. Other (please specify)
6. [If 15a]: When to you think the videos on eating and drinking and pain assessment are appropriate to share with family members?
7. Hospice admission visit
8. As issues related to eating and drinking and/or pain assessment arise
9. Other (please specify)
10. [If 15b or 15c] When do you think these videos are appropriate for hospice nurses and social workers to view? (check all that apply)
11. Onboarding for new hires
12. Annually
13. Twice a year
14. >2 times a year (specify how often)
15. These videos are not appropriate for hospice nurses and social workers
16. Thinking about the videos: there are 4 educational videos. Do you think that is:
    1. Too many videos
    2. An acceptable number of videos
    3. Not enough videos
17. If you could choose, what would be your preferred way to view the videos?
    1. On your own
    2. In a small group setting
    3. As part of clinical team meetings
    4. Other (please explain)

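### The skip rule after the video-difficulty item misroutes clinicians in the listed answer order, and a reverse-code mark on one of five identically scaled difficulty items makes clinician and care partner ease scores run opposite ways

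*Protocol*

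**What the plan says.** All the items are in the Protocol Appendix and serve Aims 2 and 3 unless noted. Five of them offer the same five answers in the same order, *Very difficult* first and *Not at all difficult* last:

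- Review of Individual Videos (clinicians): "How difficult was it for you to understand the content of the video on [insert /topic".
- The same review, questions on all videos together (Aim 3 only): "How difficult was it to view the videos using your preferred method".
- Review of [Assessment Tool/Worksheet] (clinicians and care partners): "How difficult was it for you to understand the content of the [assessment tool/worksheet".
- Post-intervention, Family Care partner: "How difficult was it to use the [assessment tool/worksheet".
- Post-intervention, Clinicians: "How difficult was it to use the [assessment tool/worksheet] as part of your clinical practice? (reverse code".

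Only the last carries a reversal mark.

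The first is followed by a conditional checklist: "If participant scores >1 on the previous item]: I am going to list a few things that may have made the video difficult to understand". The matching checklist in the tool review has no condition.

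The helpfulness items run upward, from *Not at all helpful* to *Very helpful*. The exception is item 8 of the tool review, on how well the video explained the tool. It runs downward through a midpoint of "Neither helpful nor unhelpful" and carries no mark.

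Analytic Methods (section 9) names a feasibility questionnaire in the Appendix as the source of participants' evaluations of utility and acceptability.

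**The concern.** A skip rule decides who is asked a question. If it points the wrong way, the people best placed to say what made a video hard are passed over, and people who had no difficulty are asked to explain one. No later analysis can recover answers that were never collected.

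A reversal mark decides what a high score means. If it is applied to one of several identically laid-out items, a table of ease scores will mix items where high is good with items where high is bad, unless someone notices. With about 12 clinicians in the intervention arm, a reversed item would be conspicuous in the feasibility results. The Aim 2 answers on the same form are used to revise the materials before the randomised pilot.

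**Working it through.** The Protocol gives no figure to reproduce here. The check is whether any one numeric coding of the shared answer list satisfies both the branch and the reversal mark.

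**Inputs.** The five answers in listed order, the condition *score > 1*, and reverse coding on a five-point scale, that is, new score = 6 − old score.

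| Answer | Coding A: as listed | Asked under > 1? | 6 − A | Coding B: opposite | Asked under > 1? | 6 − B |
|---|---|---|---|---|---|---|
| Very difficult | 1 | **no** | 5 | 5 | yes | 1 |
| Difficult | 2 | yes | 4 | 4 | yes | 2 |
| Moderately difficult | 3 | yes | 3 | 3 | yes | 3 |
| Slightly difficult | 4 | yes | 2 | 2 | yes | 4 |
| Not at all difficult | 5 | **yes** | 1 | 1 | no | 5 |

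**Coding A.** The branch fails at both ends: the worst answer is skipped and the best is asked. High already means easy, so reversing the clinician post-intervention item makes high mean hard on that item, while on the other four high still means easy.

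**Coding B.** The branch works, and the mark is sensible because it turns a hard-is-high item into an easy-is-high one. But the other four items, with the same answer list, carry no mark and stay hard-is-high.

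**Clinician against care partner.** Under either coding, two items with the same list end up in opposite directions when one is reversed and the other is not. Under A, *Not at all difficult* scores 1 for clinicians and 5 for care partners; under B it scores 5 and 1. This conclusion does not depend on which coding was intended.

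**Illustration with assumed answers.** Suppose 12 clinicians answer the post-intervention item, coded as listed, with five 5s, four 4s, one 3, one 2 and one 1.

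- Unreversed: the top two categories hold 9/12 = 75%, and the mean is (25 + 16 + 3 + 2 + 1)/12 = 47/12 = 3.92.
- Reversed as marked, then read as though high meant easy: the top two hold 2/12 = 17%, and the mean is 6 − 3.92 = 2.08.

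These figures show how far one item could move. They are not a forecast.

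**The case against.** The strongest reply is that the document assigns no numeric code to these answers. Other skip rules in the Appendix refer to options by letter (for instance 2b or 2c in the video review), and one list in the tool review is printed a to e. The digits may therefore be list positions produced when the PDF was read. Coding B would then reconcile the branch with the mark, leaving only an annotation not repeated on four items, which a codebook or analysis plan could settle.

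Part of this stands: the codes are not stated, and the digits should not be leaned on. But if the options are lettered, a rule written as *greater than 1* has no defined meaning for whoever programs the survey. Coding B still leaves the mark on one of five identical lists. The branch is also a rule for administering the survey, which an analysis plan cannot mend afterwards.

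Three stronger readings are tempting, and the document does not support them:

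- **That clinicians with the most difficulty are never asked why.** The branch governs only a yes/no checklist about videos. In the same review everyone is asked how to improve the video, what more information would help and what questions remain. For the tool, the checklist has no condition, and the clinician post-intervention form asks openly what made it difficult to use.
- **That the >70% criteria could be reported backwards.** The Aim 3 hypotheses name training completion, use as intended, usefulness and satisfaction. Difficulty is not among them, and the satisfaction and general helpfulness items all run upward.
- **That usefulness is scored backwards through the descending helpfulness item.** Its labels are clear, and it concerns only how well one video explained the tool. It would mislead only if pooled, or cut at the same codes, with the other helpfulness items. It is an inconsistency, not a contradiction.

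The Protocol also describes no composite ease score and no formal comparison of clinicians with care partners, so the harm from the mark lies in reading and tabulating the scores.

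**Conclusion.** The point holds in a limited form. Applied in the listed order, the branch withholds the structured causes checklist from the one answer level it most needs to reach and offers it to the one level for which it makes no sense. The reversal mark, as placed, makes clinician and care partner ease of use run in opposite directions under any common coding. No single coding makes the branch, the lone mark and the four unmarked items agree.

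The reach is the video checklist and the direction of the ease scores. The Zarit burden outcome and the power calculation are not affected. Miscoding can be corrected as long as answer labels are stored; checklist answers that were skipped cannot.

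The verdict assumes that the answer order is as listed and that identical lists receive identical codes. If different codes were intended for identical lists, the Protocol does not say so. This is a modest defect, worth correcting because correction is so cheap.

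**What to change.** 1. Reword the branch after the video-content item by label: ask the checklist after any answer other than *Not at all difficult*.
2. State one numeric code and one direction for the shared difficulty list, and apply it to all five items in both groups. If high is to mean easy and the list is coded as printed, no reversal is needed and the mark on the clinician item should go. If the opposite code is kept, the mark belongs on all five.
3. As a tidy-up, list item 8 of the tool review from *Not at all helpful* to *Very helpful*, or mark it for reversal.

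The cost is a few survey and codebook edits. For data already collected, check how the branch was programmed, recode difficulty answers from their labels, and report how many clinicians were skipped by the checklist.

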**Evaluation Items for Continuing Education**

License number [Collected for individuals qualifying for continuing education for which license numbers are required]

Asked of all continuing education participants

*(repeated for each module)*

- 1. Indicate how you received this training:
     - 1. Live (in person or via zoom)
       2. Pre-recorded
       3. Online activity
     1. Please rate the speaker’s:
        1. Knowledge of subject
           - Excellent
           - Good
           - Fair
           - Poor
        2. Clarity of Content
           - Excellent
           - Good
           - Fair
           - Poor
        3. Effectiveness teaching
           - Excellent
           - Good
           - Fair
           - Poor
     2. Rate the degree to which the activity achieved stated learning objectives:
        1. Excellent
        2. Good
        3. Fair
        4. Poor

3a. Please explain [text box]

- - 1. Rate the content of the activity
       1. Excellent
       2. Good
       3. Fair
       4. Poor

4a. Please explain [text box]

- - 1. Rate the convenience of the schedule during which the activity was provided
       1. Excellent
       2. Good
       3. Fair
       4. Poor

Please explain [text box]

- - 1. Did you identify bias during the activity?
       1. No
       2. Yes (please explain)
    2. Overall how would you rate this activity?
       1. Excellent
       2. Good
       3. Fair
       4. Poor

## **FCP Post-Visit Fidelity Assessment Form** To be distributed to FCP following a visit with an enrolled clinician)

Our records indicate [insert enrolled clinician name] from VNS Health visited with your loved one on [insert date]. Thank you for answering the following question[s] about that visit.

1. [Control arm only] Please choose the option that best describes your interaction with [insert enrolled clinician name]:
   1. I did not speak with the clinician during the visit.
   2. We discussed what was happening with my loved one.
   3. We discussed what was bothering me.
   4. We discussed what was happening with my loved one and what was bothering me.
   5. Other (please explain)
2. [Intervention arm only]. Please choose the option that best describes your interaction with [insert enrolled clinician name].
   - - 1. I did not speak with [him/her/the nurse/the social worker/the clinician] during the visit.
       2. I spoke with [him/her/the nurse/the social worker/the clinician], but we did not discuss what was bothering me.
       3. We discussed what was bothering me and completed a worksheet together.
       4. We discussed what was bothering me and [she/he] left a worksheet for me to complete.
       5. We discussed what was bothering me.
       6. Other (please explain)

[Intervention arm only, if response to 2 is c or d] NOTE: final language will be adjusted to reflect words that are used to describe different components of the [tool/worksheet] based on feedback from Round 2 of Aim 1.

1. Did you have any issues completing the worksheet?
2. No
3. Yes (please explain)
4. Did you talk about different strategies to deal with what is bothering you?
   1. No
   2. Yes
5. Did you talk about pros and cons of the different strategies?
   1. No
   2. Yes
6. Do you decide on a strategy to follow?
   1. No
   2. Yes
7. Do you plan to follow the strategy?
   1. No
   2. Yes

Why or why not?

